**Figure 2 F2:**
[figure not shown]
**Flowchart for the protocol for manual intramuscular needle placement checked by PSRM as verified by means of ES.** Whether or not the needle is positioned correctly after manual intramuscular needle placement checked by PSRM; the needle at this stage will not be removed or repositioned. ES will be initiated at 1.50 mA. A palpable and visible contraction of only the target muscle will be assessed as an ES-true verification. The ES level will be reduced to 1.00 mA if more than one muscle contracts at the same time. If only the target muscle shows a palpable and visible contraction after the ES level is reduced, the needle location will be defined as an ES-true verification. Contraction of a different muscle will be assessed as ES-false verification. When there is no contraction at all, the current will be increased to a maximum of 5.0 mA. If there is still no muscle contraction or a different muscle contracts, or many muscles contract at the same time, this will be defined as an ES-false verification.

All data will remain anonymous, to everyone except the principal investigator.

### Statistical analysis

Analyses will be performed using the Statistical Package for the Social Sciences, version 15.0 (SPSS, IBM, New York, USA). The main object of the analysis will be the contingent table of manual intramuscular needle placement checked by PSRM observations versus the corresponding verification as by means of ES observations (see Table 1). This table will be used to calculate the positive predictive value (PPV), with its confidence interval of 95%, as the main objective for each individual muscle and muscle injection location. Positive predictive value or precision is defined as the proportion of the PSRM true positive observations against all the positive observations, both PSRM true positive and PSRM observations. A PPV of 80% with 95% confidence interval and a lower bound of 70% is defined as a minimal acceptable proportion. In addition, negative predictive value (NPV), sensitivity and specificity will also be computed, with their confidence intervals of 95%.

**Table 1 T1:** Contingent table of manual intramuscular needle placement checked by PSRM observations versus the corresponding observations with ES

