### Sample size calculation

Each individual muscle injection location of the ADB, ADL, GR, SEM, SET, BF, RF, GL, GM and SO after manual intramuscular needle placement checked by PSRM will be investigated by ES to determine correct needle placement.

The positive predictive value (PPV) or precision is clinically the most relevant parameter to assess the value of this manual intramuscular needle placement checked by PSRM, as it indicates the proportion of the true positive needle placements in the intended muscle against all, true and false, positive needle placements in the intended muscle. If we assume that 90% of the test outcome of manual intramuscular needle placements observed after PSRM is determined to be positive, with α = 0.05 and a power of 80%, then 41 observations of a positive manual intramuscular needle placement will be required for the injection location for each individual muscle. If we assume that approximately 70% of the test outcome of manual intramuscular needle placements observed after PSRM is determined to be positive, with α = 0.05 and a power of 80%, then a total of 60 observations of a positive manual intramuscular needle placement will be required for the injection location for each individual muscle.

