		**Electrical stimulation**		
		**ES-true**	**ES-false**	
**Protocol for manual intramuscular needle placement checked by PSRM**	PSRM-positive	*True positive*	*False positive*	**PPV or precision**
	PSRM-negative	*True negative*	*False negative*	NNP
		Sensitivity	Specificity	Accuracy

This table will be used to calculate the positive predictive value (PPV), with its confidence interval of 95%, as the main objective for each individual muscle and muscle injection location. The positive predictive value or precision is defined as the proportion of true positive results against all the positive results, both true positives and false positives. In addition, negative predictive value (NPV), sensitivity and specificity will also be computed, with their confidence intervals of 95%.

The measures of association (odds ratios) will be compared with Cochran’s test for homogeneity. Factors which might be related to a false positive intramuscular needle placement checked by PSRM, such as type of target muscle, injection location in the different target muscles, left and right legs, gender, height, weight, body mass index, age and level of experience of the doctor will be assessed by means of a multifactorial analysis of variance.

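### The PPV intervals and the 41/60 sample size count placements as independent although one child can supply several, so the 70% lower-bound rule is met somewhat too often

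*Protocol article*

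**What the plan says.** In the protocol article, Statistical analysis makes the cross-table of PSRM result against ES result the main object of analysis, with the placement as its unit. On the PPV it says: "This table will be used to calculate the positive predictive value (PPV), with its confidence interval of 95%, as the main objective", for each muscle and each muscle injection location. NPV, sensitivity and specificity get 95% intervals from the same table. A PPV of 80% with a lower bound of 70% is the minimum acceptable, and the Discussion ties suitability for clinical practice to that rule.

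The paragraph after Table 1 adds two analyses. One is a homogeneity test: "The measures of association (odds ratios) will be compared with" Cochran's test. The other is a multifactorial analysis of variance of factors behind false positives. These include target muscle, injection location and "left and right legs, gender, height, weight, body mass index, age and level of experience of the doctor".

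Sample size calculation also counts placements. At an assumed 90%, "then 41 observations of a positive manual intramuscular needle placement will be required for the injection location for each individual muscle"; at about 70%, "then a total of 60 observations of a positive manual intramuscular needle placement will be required". Neither figure is stated in children.

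Methods lists ten muscles and refers to different injection locations within a muscle. Nothing limits a child to one placement per table, and the article does not mention within-child correlation.

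**The concern.** Placements in the same child share that child's age, height, weight, body mass index, gender and anatomy. The plan itself names most of these as possible causes of false positives, so its own reasoning predicts that results within a child are correlated.

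Two levels are affected. At a single location a child can supply a left and a right placement. In a muscle-level table the same child can supply several locations on both legs. In either case 60 placements carry less information than 60 independent observations, and an interval from the table counts is too narrow.

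This matters because the lower bound is the decision. An interval that is too short lets a location with an inadequate PPV be called precise. Tests of child-level factors in the analysis of variance are too liberal for the same reason, since each child's covariates are counted once per placement.

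**Working it through.** **The plan's own figures.** Inputs from Sample size calculation: "with α = 0.05 and a power of 80" per cent, assumed proportions 90% and about 70%, required n 41 and 60. No null value, sidedness or precision target is given, so neither figure can be derived from what is stated. An assumed null of 0.75, one-sided, comes close to the first:

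((1.645·√(0.75·0.25) + 0.842·√(0.90·0.10)) / 0.15)² = 41.4.

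For 70%, a null of 0.50 gives 46.6 two-sided or 36.5 one-sided, and a null of 0.55 gives 82.3 or 64.4. None is 60. This is a separate matter. What counts here is that no variant tried needs or contains a clustering term. The stated 41 and 60 are used below as they stand.

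**Assumptions.** The documents give neither the number of positive placements per child in a table (m) nor the ICC. For one location I take m=2 (left and right) and ICC 0.1 to 0.5. For a muscle-level table I take m=4 (for example two locations on two legs), mainly with ICC 0.1 to 0.3. The interval method is not stated, so Wilson is the main case.

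**Design effect.** DE = 1 + (m − 1)·ICC.
- m=2: DE is 1.1, 1.3, 1.5 at ICC 0.1, 0.3, 0.5. Sixty placements are then worth 60/1.1 = 55 down to 60/1.5 = 40.
- m=4: DE is 1.3 and 1.9 at ICC 0.1 and 0.3.
- To keep the information of 41 / 60 independent observations, multiply by DE. For m=2 this gives 46 / 66, 54 / 78 and 62 / 90. For m=4 it gives 54 / 78 and 78 / 114.

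**One data set, two answers.** With n=41, 34 ES-true placements give 34/41 = 82.9%. The Wald bound for independent data is 0.829 − 1.96·√(0.829·0.171/41) = 71.4%, a pass. Multiplying the variance by 1.3 gives 69.8%, and by 1.5 gives 68.8%, both fails. With n=60, 49/60 = 81.7% gives 71.9% for independent data, 70.5% at DE 1.3 and 69.7% at DE 1.5.

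**How often the rule is met when the true PPV is only 70%.** The count of true positives is the sum over children of beta-binomial variables with mean 0.70 and the given ICC, convolved exactly. Passing means a PPV of at least 80% and a lower bound of at least 70%, computed as if placements were independent. With Wilson limits this requires 35/41 or 49/60.

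| n | m | ICC | False pass | Coverage of the 95% interval |
|---|---|---|---|---|
| 41 | 1 | – | 1.9% | 96.1% |
| 41 | 2 | 0.1 / 0.3 / 0.5 | 2.4% / 3.5% / 4.6% | 95.1% / 93.0% / 90.8% |
| 60 | 1 | – | 2.9% | 93.4% |
| 60 | 2 | 0.1 / 0.3 / 0.5 | 3.6% / 4.9% / 6.3% | 92% / 89% / 87% |
| 60 | 4 | 0.1 / 0.3 | 4.9% / 8.8% | 89% / 82% |

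A Wald interval gives the same false-pass rates at n=60. At n=41 it is worse: 4.6% if independent, then 5.4% / 7.0% / 8.6% for m=2. An exact binomial interval has the same pass mark as Wilson at n=41 and so the same rates.

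**The case against.** The best defence is that the article names no interval formula, and that a condensed protocol article may leave the variance estimator to an analysis plan that is not shown. Independence is indeed implied rather than stated. But the article does fix the table as the source of the interval, the placement as the unit of the sample size, and two further methods that, as named, assume independent observations. The point concerns those stated choices.

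The second defence is size, and much of it stands. The Discussion rejects combining muscles and locations, so the per-location PPV carries most weight. There a child gives at most two placements per session, and children injected on one side lower the design effect further. At n=41 with ICC 0.1 the false-pass rate is 2.4%, still below a one-sided 2.5%. At n=60 Wilson coverage is already 93.4% without clustering, so clustering does not explain the whole shortfall from 95%.

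Three stronger readings are tempting and should be resisted.
- A reader might infer that every planned test is too liberal. For contrasts within a child (left against right, muscle against muscle, location against location), ignoring a positive correlation can make a test conservative. Cochran's test wrongly treats strata containing the same children as independent, but its error could go either way, and no calculation here shows which.
- A reader might take it that one doctor makes all of a child's placements in one session. The document does not say so. It lists only the doctor's level of experience as a factor.
- A reader might conclude that 41 and 60 fall short by a known amount. They do not, because m and the ICC are unknown.

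**Conclusion.** The point holds for the PPV intervals, and likewise for NPV, sensitivity and specificity. As planned they are too narrow under any positive within-child correlation, and the 70% rule is met too often. The direction needs only that correlation and some children with more than one placement in a table. The size depends on the assumed m, ICC and interval method.

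Per location the effect is modest. It is larger for a muscle-level PPV, which the Statistical analysis section also names as a main objective. Tests of age, height, weight, body mass index and gender are too liberal. Left/right, muscle and location comparisons and Cochran's test rest on a wrong independence assumption, with an error of unknown direction. The stated 80% power applies to independent observations and is lower when children contribute more than one.

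The change should be made before results are seen, because it alters the interval that decides the primary question.

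**What to change.** - Compute every PPV, NPV, sensitivity and specificity interval with the child as cluster. Either a bootstrap that resamples children or a GEE logistic model with small-sample-corrected robust errors will do. The correction is needed because 60 placements at two or four per child come from only 30 or 15 children.
- Apply the 70% lower-bound rule to that interval.
- Replace the analysis of variance and the independent-strata homogeneity test with a logistic model for the ES result that accounts for the child.
- Report the number of children beside the number of placements in each table.
- State in Sample size calculation that 41 and 60 are effective, independent observations. Either inflate them by a design effect with a stated m and ICC, or say plainly that power is below 80% when children contribute more than one placement.

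No new measurements are required, only a coded child identifier kept with each placement, which is compatible with the anonymity statement. The price is somewhat wider intervals, lower power at the same number of placements, and possibly some locations that no longer pass. Inflating the sample size to restore power would mean more recruitment.

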		**Electrical stimulation**		
		**ES-true**	**ES-false**	
**Protocol for manual intramuscular needle placement checked by PSRM**	PSRM-positive	*True positive*	*False positive*	**PPV or precision**
	PSRM-negative	*True negative*	*False negative*	NNP
		Sensitivity	Specificity	Accuracy

This table will be used to calculate the positive predictive value (PPV), with its confidence interval of 95%, as the main objective for each individual muscle and muscle injection location. The positive predictive value or precision is defined as the proportion of true positive results against all the positive results, both true positives and false positives. In addition, negative predictive value (NPV), sensitivity and specificity will also be computed, with their confidence intervals of 95%.

The measures of association (odds ratios) will be compared with Cochran’s test for homogeneity. Factors which might be related to a false positive intramuscular needle placement checked by PSRM, such as type of target muscle, injection location in the different target muscles, left and right legs, gender, height, weight, body mass index, age and level of experience of the doctor will be assessed by means of a multifactorial analysis of variance.

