### Study procedures

All children will receive their planned BTX-A treatment under general anaesthesia in the operating rooms of the VU University Medical Centre. The protocol for manual intramuscular needle placement checked by PSRM will be used (see Additional file 1).

A 25 mm or 50 mm Stimuplex needle will be used for the injection. Manual intramuscular needle placement will be assessed as a PSRM-positive verification when the needle moves upon passive stretching and relaxing of the intended muscle. Manual intramuscular needle placement will be defined as a PSRM-negative verification when there is no movement or only a small straight movement of the needle upon passive stretching and relaxing of the muscle (see Figure 1). Whether or not the needle is positioned correctly, it will at this stage not be removed or repositioned.

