**Figure 1 F1:**
[figure not shown]
**Flowchart for the protocol for manual intramuscular needle placement checked by PSRM.** Manual intramuscular needle placement checked by PSRM will be assessed as a PSRM-positive verification when the needle moves upon PSRM. Manual intramuscular needle placement will be defined as a PSRM-negative verification when there is no movement or only a small straight movement of the needle upon PSRM.

The needle location will then be verified by means of a Stimuplex HNS 12 electrical stimulator. ES will be initiated at 1.50 mA. A palpable and visible contraction of only the target muscle will be assessed as an ES-true verification. The ES level will be reduced to 1.00 mA if more than one muscle contracts at the same time. If only the target muscle shows a palpable and visible contraction after the ES level is reduced, the needle location will be defined as an ES-true verification. Contraction of a different muscle will be assessed as ES-false verification. When there is no contraction at all, the current will be increased to a maximum of 5.0 mA. If there is still no muscle contraction or a different muscle contracts, or many muscles contract at the same time, this will be defined as an ES-false verification. A palpable and visible contraction of only the target muscle is defined as an ES-true verification (see Figure 2). After this procedure, regular BTX-A treatment will be continued and the needle can be readjusted if necessary.

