Clarifying statistical terms used in a manuscript is of great importance to make a clear interpretation of the results. In this study protocol the main object of analysis will be the contingent table of intramuscular needle placement checked by PSRM observations versus the corresponding observations with ES (see Table 1). This table will be used to calculate the precision or PPV which is defined as the proportion of true positive needle placements against all positive needle placement results (both true positives and false positives). During BTX-A treatment, BTX-A should be injected only after manual intramuscular needle placement checked positive by PSRM, ES or echo using a verified protocol.

In this study protocol the statistical term accuracy is defined as the proportion of true needle placements (both true positives and true negatives). In a similar article the authors calculated the accuracy which was defined differently as the proportion of positive needle placements checked by ES out of all manual intramuscular injections. Negative manual intramuscular needle placements were not investigated and not checked by ES [16]. One article described intramuscular needle placement based on only landmarks and palpation and in a randomized clinical trial needle placement was based on palpation of the muscle belly after increasing muscle tone by stretching the spastic ankle plantar flexors. Both studies did no use a PSRM technique or an other verification technique to localize the correct needle placement in the target muscle [18,21]. The three methodological methods used do not allow the construction of a contingent table of intramuscular needle placements checked by a needle location technique observations versus observations verified as by means of ES or echo. Nor do they allow the calculation of positive predictive values or precision with their confidence intervals as the main objective for each individual muscle and muscle injection location neither the calculation of the negative predictive value, sensitivity and specificity. This obscures the outcome and allows no clear answer to the question whether intramuscular needle placement is precise for a specific target muscle and a specific injection location.

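### Table 1 reverses the true-negative and false-negative labels in the PSRM-negative row, so NPV and accuracy, and other secondary measures built from those labels, would be miscalculated

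*Protocol article*

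**What the plan says.** The index test is needle movement on passive stretching and relaxing of the muscle (PSRM). Under Study procedures: "Manual intramuscular needle placement will be defined as a PSRM-negative verification when there is no movement or only a small straight movement of the needle". The reference is ES. In the same section: "A palpable and visible contraction of only the target muscle is defined as an ES-true verification", and "Contraction of a different muscle will be assessed as ES-false verification".

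Table 1 crosses the two. Its PSRM-positive row reads true positive (ES-true) and false positive (ES-false). Its PSRM-negative row reads "True negative" (ES-true) and "False negative" (ES-false). The margin below puts sensitivity under the ES-true column, specificity under the ES-false column and accuracy in the corner. The margin beside the PSRM-negative row reads NNP, evidently meant as NPV.

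The text under the table makes PPV the main objective, then adds: "In addition, negative predictive value (NPV), sensitivity and specificity will also be computed, with their confidence intervals of 95" per cent. The Discussion defines accuracy through the cell names: "accuracy is defined as the proportion of true needle placements (both true positives and true negatives"). The plan also compares odds ratios with Cochran's test for homogeneity.

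**The concern.** A negative result is true when the reference agrees that the needle is not in the target, and false when the reference shows that it is. Table 1 prints the opposite in both cells of the PSRM-negative row. Each label seems to have been formed by joining the column word (true or false) to the row word (positive or negative). That gives the right names in the positive row and the wrong ones in the negative row.

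This table is what the measures are to be computed from, and the article gives no written formula for NPV, sensitivity or specificity that would override the labels. Accuracy is defined only through the labels. At stake are the secondary measures for each muscle and injection location, and any odds ratio put together from the named cells.

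**Working it through.** **Inputs.** From the protocol: the definitions of PSRM-positive/negative and ES-true/false (Study procedures), the cell labels and margins (Table 1), and the definition of accuracy (Discussion). The protocol states no cell counts and no figure to reproduce, so all counts below are assumptions chosen to show a range.

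**Notation.** a = PSRM-positive/ES-true, b = PSRM-positive/ES-false, c = PSRM-negative/ES-true, d = PSRM-negative/ES-false, N = a+b+c+d.

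**Step 1: which label is right.** In cell c, only the target muscle contracts, so the needle is in the target, but the PSRM check was negative. That is a false negative. In cell d, ES does not confirm the target and the check was negative. That is a true negative. So FN = c and TN = d, whereas the table prints TN = c and FN = d.

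**Step 2: cells against margins.** Sensitivity under the ES-true column needs TP and FN in that column, and specificity under the ES-false column needs FP and TN in that one. The printed labels put TP with TN in the first and FP with FN in the second. Cells and margins cannot both be right; the margins agree with step 1.

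**Step 3: formulas, correct and as labelled.**

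| Measure | Formula | Correct | As labelled |
|---|---|---|---|
| PPV | TP/(TP+FP) | a/(a+b) | a/(a+b) |
| NPV | TN/(TN+FN) | d/(c+d) | c/(c+d) = 1 − NPV |
| Sensitivity | TP/(TP+FN) | a/(a+c) | a/(a+d) |
| Specificity | TN/(TN+FP) | d/(b+d) | c/(b+c) |
| Accuracy | (TP+TN)/N | (a+d)/N | (a+c)/N |
| Odds ratio | TP×TN/(FP×FN) | ad/(bc) | ac/(bd) |

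As labelled, the accuracy numerator a+c is the whole ES-true column, so the measure no longer depends on the PSRM result at all.

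**Step 4: assumed counts.**

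*(a,b,c,d) = (46,8,1,5), N = 60*
- NPV: 5/6 = 83.3% correct; 1/6 = 16.7% as labelled
- Sensitivity: 46/47 = 97.9%; 46/51 = 90.2%
- Specificity: 5/13 = 38.5%; 1/9 = 11.1%
- Accuracy: 51/60 = 85.0%; 47/60 = 78.3%

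*(33,8,3,2), N = 46*
- NPV: 2/5 = 40%; 3/5 = 60%
- Sensitivity: 33/36 = 91.7%; 33/35 = 94.3%
- Specificity: 2/10 = 20.0%; 3/11 = 27.3%
- Accuracy: 35/46 = 76.1%; 36/46 = 78.3%
- Odds ratio: (33×2)/(8×3) = 2.75; (33×3)/(8×2) = 6.19

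*(48,12,2,8)*
- Odds ratio: (48×8)/(12×2) = 16.0; (48×2)/(12×8) = 1.0

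*(48,12,5,5)*
- c = d, so every measure is the same under either labelling.

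The error lowers every affected measure in the first set and raises every one in the second. PPV is identical under either labelling in all four.

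**The case against.** A reader might infer that NPV, sensitivity, specificity and accuracy will all come out wrong. The document does not support that. PSRM and ES results are each defined without ambiguity, so the raw data can be coded correctly whatever the cells are called. The column margins are in the right place: an analyst who divides down the ES-true column gets a/(a+c), and down the ES-false column d/(b+d), both correct. An odds ratio taken from the cross-tabulation by position is also right. And the two labellings agree when c = d. What stands against this is that the row margin does not say which cell is the numerator of NPV, and that accuracy is defined by label. Those two measures are the most exposed.

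A reader might also infer that the trial's main result is at risk. It is not. PPV, its acceptability criterion (80% with a lower bound of 70%) and the sample size reasoning rest on the PSRM-positive row, which is labelled correctly. The other measures carry no threshold, and accuracy is not among those listed for computation with confidence intervals.

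A third tempting reading is that mislabelled accuracy becomes exactly the measure that the Discussion sets apart from its own, namely ES-positive placements out of all manual injections in an earlier study. The form is similar, but the Discussion says that negative placements were not checked by ES in that study, whereas (a+c)/N here includes PSRM-negative placements that were. The match is close, not exact.

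Lastly, the sentence defining PPV in the Statistical analysis text has an incomplete denominator, but the note under Table 1 and the Discussion both give it in full. It is an editorial slip and adds no weight.

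**Conclusion.** The point holds in limited form. The two labels in the PSRM-negative row are reversed under the protocol's own definitions, and they contradict the table's own margins. For anyone who follows the labels, NPV turns into its complement and accuracy into the ES-true share. Sensitivity, specificity and label-built odds ratios are then also wrong unless the two PSRM-negative cells are equal.

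The size cannot be fixed from the document. Over the two assumed sets of percentages above, NPV moves from 83.3% to 16.7% in one and from 40% to 60% in the other, and accuracy from 85.0% to 78.3% and from 76.1% to 78.3%. Both size and direction depend on how the PSRM-negative placements split between ES-true and ES-false.

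This should be fixed. It is a wrong definition in the table that underlies the analysis, but its reach is confined to secondary measures.

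**What to change.** In Table 1, swap the two labels: PSRM-negative/ES-true becomes false negative, and PSRM-negative/ES-false becomes true negative. Beside or below the table, state the formulas on the corrected cells:

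- NPV = TN/(TN+FN), across the PSRM-negative row
- sensitivity = TP/(TP+FN), down the ES-true column
- specificity = TN/(TN+FP), down the ES-false column
- accuracy = (TP+TN)/all placements

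The row margin printed as NNP can be corrected to NPV at the same time. The cost is an edit to one table and its note. Design, sample size, data collection and the PPV criterion do not change.

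### The factor analysis for false-positive placements uses ANOVA on a yes/no result per needle and ignores that needles share a child and a doctor, so tests of child-level and doctor-level factors are prone to be anti-conservative

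*Protocol article*

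**What the plan says.** The Statistical analysis section of the protocol article, in the paragraph after Table 1, sets out a search for explanations of wrong placements. The outcome is given as "Factors which might be related to a false positive intramuscular needle placement checked by PSRM". The candidate factors are introduced as "such as type of target muscle, injection location in the different target muscles", and the list continues with "left and right legs, gender, height, weight, body mass index, age and level of experience of the doctor". The method is fixed in the same sentence: these factors "will be assessed by means of a multifactorial analysis of variance".

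Three other places show what the data will look like.

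- Study procedures makes the reference result two-valued for each needle: "A palpable and visible contraction of only the target muscle will be assessed as an ES-true verification", and the other listed responses count as ES-false.
- Sample size calculation covers ten muscles: "Each individual muscle injection location of the ADB, ADL, GR, SEM, SET, BF, RF, GL, GM and SO".
- The same section counts needles, not children: "then 41 observations of a positive manual intramuscular needle placement will be required for the injection location for each individual muscle". Under its second assumption, "then a total of 60 observations of a positive manual intramuscular needle placement will be required".

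The article names no child or doctor effect, repeated-measures structure, clustered variance or logistic model.

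**The concern.** A false positive is a needle that is PSRM-positive and ES-false, so the outcome is 0 or 1. Muscle, location and leg vary from needle to needle within a child and enter the same model as gender, age and body size. The data row must therefore be the needle, and a child treated in several muscles or both legs supplies several rows.

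Gender, age, height, weight and BMI take one value per child, and experience takes one value per doctor at a given time. An ordinary ANOVA tests them as though each needle were an independent child or doctor. If needles in the same child, or placed by the same doctor, tend to succeed or fail together, the standard errors for these factors are too small.

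What is at stake is the explanation of where PSRM fails. A chance association with age, body size or doctor experience could be reported as real. The last bears on who can rely on the technique.

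**Working it through.** **No planned figure to reproduce.** The article attaches no number to this ANOVA. Its 41 and 60 observations belong to the PPV objective, and the argument does not depend on them.

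**Inputs.** From the article: a binary outcome per needle, ten muscles with injection locations, both legs, child-level and doctor-level factors, and ANOVA as the method. Assumed, because the article is silent: m = 4, 8 or 16 placements per child; within-child ICC 0.05, 0.10 or 0.20; 60 children; false-positive rates of 10%, 20% and 30%; 2, 4 or 6 doctors with between-doctor ICC 0.01 to 0.05.

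**Step 1: the binary outcome alone.** The variance is p(1−p): 0.09 at 10%, 0.16 at 20% and 0.21 at 30%, a ratio of 0.21/0.09 = 2.3 across that range. To see whether this distorts p-values, 0/1 data were simulated without clustering (one placement per child, or eight with ICC 0; 3,000 runs per setting) and analysed by ordinary least squares with age, sex and leg. The 5% test for age rejected in 4.5% to 5.8% of runs. The binary outcome did not by itself inflate the error in these settings.

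**Step 2: child-level factors with clustering.** Design effect DE = 1 + (m − 1) × ICC. True two-sided error of a nominal 5% test = 2 × [1 − Φ(1.96/√DE)]. For example, with m = 8 and ICC 0.10, DE = 1 + 7 × 0.10 = 1.70; 1.96/√1.70 = 1.50; error = 0.133. The simulation drew clustered 0/1 outcomes (beta-binomial) with no true age effect. Results at a 20% false-positive rate:

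| m | ICC | DE | Error, formula | Error, simulated (age) |
|---|---|---|---|---|
| 4 | 0.05 | 1.15 | 0.068 | 0.069 |
| 4 | 0.10 | 1.30 | 0.086 | 0.073 |
| 4 | 0.20 | 1.60 | 0.121 | 0.122 |
| 8 | 0.05 | 1.35 | 0.092 | 0.097 |
| 8 | 0.10 | 1.70 | 0.133 | 0.134 |
| 8 | 0.20 | 2.40 | 0.206 | 0.214 |
| 16 | 0.05 | 1.75 | 0.138 | 0.133 |
| 16 | 0.10 | 2.50 | 0.215 | 0.217 |
| 16 | 0.20 | 4.00 | 0.327 | 0.334 |

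Over all three false-positive rates the simulated error ran from 0.060 to 0.337. The same clustered data reduced to one mean per child gave 0.044 to 0.057, so the excess comes from treating needles as independent.

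**Step 3: a within-child factor.** In the same clustered runs the test for leg rejected in 2.4% to 5.1%. It is not inflated and is somewhat conservative as the ICC rises.

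**Step 4: doctor experience.** Assume 480 placements shared equally, experience at two levels and a 20% false-positive rate. The design effect now uses placements per doctor: with 2 doctors and ICC 0.01, DE = 1 + 239 × 0.01 = 3.39. Simulated error over ICC 0.01 to 0.05 was 0.30 to 0.60 with 2 doctors, 0.20 to 0.45 with 4, and 0.15 to 0.39 with 6.

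**The case against.** The strongest reply is that little hangs on this analysis. The article's main objective is the PPV for each muscle and injection location, judged against 80% with a lower bound of 70%, and that rule does not use the ANOVA. The factor list is open-ended, and a condensed article may leave the exact model terms to a fuller plan. The inflation also rests on quantities the article does not give: at 4 placements per child and an ICC of 0.05 it is close to nominal.

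Most of this stands, and it limits severity and certainty. It does not remove the point. The method is named, not left open, and a multifactorial ANOVA as named carries no allowance for shared children or doctors.

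Three stronger readings are tempting and are not supported.

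- A reader might infer that the yes/no outcome itself makes the p-values invalid. Step 1 does not bear this out. The binary outcome is a reason to prefer another model (unequal variance, fitted values that can leave the 0 to 1 range, no odds ratios), not the source of the inflation.
- A reader might infer that chance factors will certainly be declared significant. With an ICC of 0 or one placement per child they would not be, beyond the nominal 5%.
- A reader might infer that there are too few false positives for the number of factors. That is a caution for a logistic model, and so for the replacement; it is not a fault of least squares.

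**Conclusion.** The point holds as a should-fix matter in a secondary analysis. The stated ANOVA suits a binary outcome poorly, and it treats needles as independent when several per child are to be expected from ten muscles, their injection locations and two legs. Tests of gender, age, height, weight, BMI and doctor experience are therefore prone to be anti-conservative.

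For child-level factors the true error of a nominal 5% test is about 6% to 34% under the assumed 4 to 16 placements per child and ICC of 0.05 to 0.20. For doctor experience it is about 15% to 60% under the assumed 2 to 6 doctors and between-doctor ICC of 0.01 to 0.05. These are illustrations over assumed ranges, not estimates for this study. A reader might also infer that the verdict on the injection protocol is undermined. It is not by this point, because the main PPV estimate and its acceptance rule are calculated without the ANOVA.

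**What to change.** Replace the ANOVA with a logistic regression of false versus true positive, restricted to PSRM-positive placements, as follows.

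- **Child:** treat as the cluster, by a random intercept or by GEE with robust variance.
- **Doctor:** treat as a random level. A fixed doctor factor would absorb experience, which is constant within a doctor, and GEE clustered on child alone does not repair the doctor-level test. If doctors are few, describe results by experience without a test.
- **Body size:** use BMI, or height and weight, but not all three, because BMI is calculated from the other two and the overlap makes their effects imprecise and hard to read.
- **Few false positives:** use a penalised fit or fewer terms.
- **Reporting:** give odds ratios with 95% confidence intervals, labelled exploratory.

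The cost is a change of wording and somewhat more programming, with no new measurements provided child and doctor identifiers are kept for each needle. Intervals for child-level and doctor-level factors will be wider.
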